### Randomisation

Participating GPs will be randomly divided in to two groups A and B, using the randomisation tool built in to REDCap. They will be given Trial General Practice Numbers (TGN) from A01-A15 (group A) and B01-B15 (group B).

Participants will be given Trial Participant Numbers (TPNs). TPNs will be generated by PREDICT (the software behind YHF) when patients are included and will be given consecutively starting from 0001. The number will be given a prefix A or B depending on which group (intervention or control) the participant’s general practice belongs to. Thus, the sequence of TPNs can vary in prefixes but will consist of unique four-digit numbers (i.e. B0001, B0002, A0003, B0004, A0005, A0006, A0007, etc.). With this method of labelling TPNs and TGNs, there is room for adjustment if the number of participants/GPs ends up being either smaller or greater than the expected 640/32 in total.

Subgroup Q will be 5–15 participants chosen deliberately from the pilot group, to ensure it represents the intervention group for use in the qualitative interviews.

### Inclusion criteria for general practices

To ensure comparability to usual care, all the included general practices must use their own routine method to take blood samples, ECG etc., before annual blood pressure control consultations.All general practices in Denmark are supposed to follow a national quality guideline and take part in continuing education. This means that the standard routine methods vary only little across the country.To ensure equal quality, all general practices must measure blood pressure using an ambulatory blood pressure device under standard conditions.To ensure comparability to usual care, inclusion and subsequent intervention must be in connection to a planned blood pressure control consultation, as part of the standard blood pressure control program (either at the time of diagnosis or as a planned annually control).

These criteria are controlled when the first author visits the practices in the start-up-faze (see chapter: ‘Practical procedure’).

### Inclusion criteria for patients

All patients must understand and read Danish and must be cognitively well functioning (be able to understand the trial information given and thus make a decision on whether to participate on acceptable grounds).The patients must have Internet access, have an email address and read their emails on regular basis (at least once a week).Patients must give informed consent before inclusion.All included patients must be diagnosed with hypertension and participate in blood pressure control consultations with their GP at least once a year.Both patients with known hypertension and those newly discovered are accepted into the trial.Patients must be aged 35–75 years.Men and women are included.Co-morbidity is allowed with a few exceptions (see exclusion criteria).

### Exclusion criteria for patients

If the patient, during the trial, no longer fulfils inclusion criteria 1 and/or 2, they are excluded from the trial.If the patient during the trial develops prolonged illness so severe that treatment of hypertension is no longer a priority, he/she will be excluded.Patients with blood pressure > 170/100 are excluded, as these patients should receive intensive blood pressure treatment regardless of their predicted risk of CVD or heart age.Pregnancy.Very high cholesterol (TCL or TCL/HDL ≥ 8).Genetic lipid disorders.If the patient is diabetic and has a complicating kidney disease.Known problems with arteries to the legs defined as:
Clinical symptoms of claudicationDiminished foot pulsesCarotid bruitsRadiological evidence of atherosclerotic arterial diseasePrior surgery/percutaneous interventionsPrior stroke or mini-stroke (TIA).Angina, prior AMI or heart-related operation.

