**Fig. 1 Fig1:**
[figure not shown]
Flow chart

After identifying the list of patients from the statistics module, the practice will review the patients with regards to the inclusion/exclusion criteria. After exclusion, an invitational letter will be sent out to the first 25 patients of those remaining on the list. The invitation will contain a specific appointment for the patient, scheduled for the inclusion consultation with their GP. The invited patients can then opt out or show up at the appointment and receive the oral and written trial participant information (see Additional file 3). The inclusion consultation will be planned before the patients’ expected annual blood pressure consultation and will be planned so they can get blood samples taken at the same time. Thereby patients will not need to go to the practice more times than usual, but the practice will need to conduct an extra GP consultation to give trial information. The participating general practices will be compensated for their extra time spent on consultation with each trial participant and for the extra time spent on reviewing the patient list with regards to inclusion/exclusion criteria.

A few days after the inclusion consultation, the participant will receive an email with a link to a questionnaire (see Additional file 2) that must be completed before the subsequent appointment with the GP. The first page of the questionnaire will be the informed consent form. If the patient answers no to the informed consent, further access to the questionnaire will be closed and the patient will be excluded from the trial.

The GP responsible for the following blood pressure control consultation will ensure that the questionnaire is filled out by the patient. GPs of the intervention group must subsequently guide their patient through YHF on their computer, uploading this individual patient’s data.

With the large number of patients with known hypertension and the compressed method of inclusion, it is expected that GPs will have enough use of the YHF program to maintain the skills and knowledge to use the program, which they will be taught by the research group before start of the project.

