The RCT will consist of a 12-month intervention period, except for participants in subgroup Q who will be interviewed six months after enrolment (t_6_) and subsequently excluded. Follow-up for all other patients will happen at the next annual blood pressure control consultation (t_12_) approximately 12 months after registration of baseline data (t_0_).

The intervention group will receive an educational email every two weeks that also includes a reminder of the project and YHF. The first email is sent out approximately two weeks after the initial blood pressure control consultation. The last email is sent out two weeks after the expected one-year follow-up blood pressure control consultation. The emails’ health educational content will reflect available information from the Danish Heart Association’s web page (www.hjerteforeningen.dk).

The GPs are asked to make sure that blood pressures are measured as a standard ambulatory blood pressure just before the annual blood pressure control (t_12_).

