### Outcome measures and statistical analysis

For continuous outcomes, i.e. blood pressure and number of GP visits, linear regression analysis of mean changes from baseline will be carried out. Ordinal regression and multinomial regression will be used for ordered and categorical outcomes, i.e. PAM13 score. Adjustments for baseline values will be made. An intention-to-treat analysis will be applied. Subgroup analyses to identify groups that especially benefit from the intervention will be performed.

Since the authors oversee the project throughout and thereby have access to all data as they are generated, analyses on outcome measures will be carried out by a blinded statistician. Data will be delivered pseudonymised to the statistician.

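### Excluding enrolled patients during the trial conflicts with the stated intention-to-treat analysis; bias between arms is possible, but its direction and size cannot be derived from the protocol

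*Protocol article*

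**What the plan says.** Two of the rules under Exclusion criteria for patients act after enrolment. The first reads "If the patient, during the trial, no longer fulfils inclusion criteria 1 and/or 2, they are excluded from the trial". The second reads "If the patient during the trial develops prolonged illness so severe that treatment of hypertension is no longer a priority, he/she will be excluded". The other entries in that list, such as the blood pressure ceiling and pregnancy, are not marked as acting during the trial and are not part of this point.

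The inclusion criteria are not numbered in the text shown. By list order, criterion 1 is "All patients must understand and read Danish and must be cognitively well functioning", and criterion 2 asks for Internet access, an e-mail address and that patients "read their emails on regular basis (at least once a week").

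Outcome measures and statistical analysis states: "An intention-to-treat analysis will be applied". It does not say how patients excluded during the trial are handled.

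On e-mail, Practical procedure states: "The intervention group will receive an educational email every two weeks that also includes a reminder of the project and YHF". The Background calls these reminders the secondary component of the intervention. E-mail also carries the questionnaires in both arms: after the inclusion consultation "the participant will receive an email with a link to a questionnaire", and Data collection repeats that questionnaire at six months.

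**The concern.** Practices are randomised, and their patients then enrol and are followed for 12 months. A rule that removes an enrolled patient because of something that happens in those 12 months makes membership of the analysed group depend on a post-randomisation event. Intention-to-treat is meant to prevent exactly that.

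The e-mail criterion needs particular care because e-mail is part of what is being tested. Patients who drop away from e-mail may also be less engaged with treatment, and the trial has more e-mail contact with intervention patients than with controls. If more such patients, or different ones, are removed in one arm, the remaining patients are no longer comparable. Enrolling 600 instead of 340 would not reduce that bias.

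**Working it through.** **Step 1: what exclusion means in this document.** Practical procedure says that the interview subgroup is seen at six months and excluded afterwards, and it assigns the 12-month follow-up to all the other patients. An excluded patient therefore has no 12-month visit. (That subgroup comes from the pilot practices. It matters here only for how the word is used.) On this usage, the rules do more than define an analysis set: they end the collection of the outcome. An analysis plan cannot restore outcomes that were never collected.

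**Step 2: is there a route to different exclusion by arm?** Fortnightly mailing over 12 months is about 52/2 = 26 e-mails to each intervention patient. The e-mails described for controls are questionnaires. This gives more occasions in the intervention arm for a patient's e-mail use to come to notice, but the article describes no such check.

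**Step 3: the size of a bias, if there is one.** Let p be the share excluded in an arm and d the mean outcome of the excluded minus that of the retained. The full-arm mean is μ = (1 − p)·r + p·(r + d) = r + p·d, so the retained mean is r = μ − p·d. With no true effect, the retained-patient contrast (intervention minus control) is

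bias = −(p_I·d_I − p_C·d_C), or −(p_I − p_C)·d when d is the same in both arms.

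The documents give neither p nor d, so all values below are assumptions. Entries are absolute shifts in mmHg, with the share of the 5 mmHg planning difference (Sample size) in brackets.

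| p_I − p_C | d = 5 mmHg | d = 10 mmHg |
|---|---|---|
| 0 points | 0 | 0 |
| 5 points | 0.25 (5%) | 0.5 (10%) |
| 10 points | 0.5 (10%) | 1.0 (20%) |
| 15 points | 0.75 (15%) | 1.5 (30%) |

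The shift favours the intervention if the excess exclusions are in that arm and those patients have higher blood pressure. It goes the other way if either sign is reversed.

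**Step 4: effect on error rates.** The article gives 120 per group for 5 mmHg, two-sided 0.05 and 90% power, but no standard deviation. Solving back gives SD = 5·√(120/2)/(1.960 + 1.282) = 11.95 mmHg. An assumed SD of 11.9 reproduces 120, and 12 gives 122. The standard error is 11.95·√(2/120) = 1.54 mmHg. Ignoring clustering, a shift of 0.5 mmHg raises the two-sided type I error from 5.0% to about 6.2%, and a shift of 1.0 mmHg raises it to about 9.9%.

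**Step 5: effect on power.** The allowance of 30 per group is 30/150 = 20%, and 120/(1 − 0.20) = 150, so those two figures agree. The article does not say whether exclusions count within that 20%. If they come on top, 150·(0.80 − e) patients remain per arm. For e = 5%, 10% and 15% that is 112.5, 105 and 97.5, with power of about 88%, 86% and 83%.

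**The case against.** The strongest reply is that exclusion here may mean the end of participation rather than deletion of data. The interview subgroup is excluded after the interview, yet its interviews are plainly kept. On that reading the rules are withdrawal rules, intention-to-treat still governs the analysis, and the handling of withdrawn patients can be left to a fuller document. This stands in part: the article does not say that data already collected are discarded. It does not remove the conflict, because under the same usage the 12-month outcome is not collected.

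A reader might also infer that the trial removes non-adherent patients from the intervention arm, keeps nearly everyone in the control arm, and so favours the tool. The documents do not support that. No monitoring of e-mail opening or reading is described. Criterion 2 concerns reading one's own e-mail weekly, so a patient who ignores the advice e-mails but reads other mail still meets it. Both arms receive e-mailed questionnaires, so failure to respond could come to notice in either.

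Nor can it be said that an unblinded GP applies the illness rule. No assessor is named, and nothing shows which way that rule would push the result.

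Finally, Data collection takes blood pressure from questionnaires, and cites records and databases for GP contacts and prescriptions. Keeping patients in the trial would therefore not by itself recover every outcome.

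**Conclusion.** The conflict is in the current text. Enrolled patients are to be excluded for events during the trial, exclusion in this document means no 12-month follow-up, and the analysis is said to be intention-to-treat. As written, these cannot all hold. The point covers loss of language or cognitive function and severe illness as well as loss of e-mail use.

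Differential exclusion is plausible because the fortnightly e-mails belong to one arm only, but its direction and size cannot be derived from the documents. The range of 0 to 1.5 mmHg in the table rests wholly on assumed differences of 0 to 15 points in exclusion and 5 to 10 mmHg in outcome. It is zero if similar patients are excluded equally. A reader who concludes that this is a per-protocol comparison that demonstrably favours the intervention goes further than the text allows. The rule is still worth changing, because outcomes not collected at 12 months may not be recoverable later.

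**What to change.** Apply inclusion criteria 1 and 2 and the severe-illness rule at enrolment only. State that a patient who later falls under one of them may stop e-mails and questionnaires, but stays in follow-up and in the intention-to-treat set, in the arm of his or her practice, unless consent is withdrawn. This concerns data collection and analysis only, not the patient's care.

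For these patients:
- Take GP contacts and prescriptions from the records and databases already named under Data collection.
- When the questionnaire is missing, obtain from the practice the ambulatory blood pressure that GPs are already asked to arrange just before the 12-month control.
- Treat missing questionnaire outcomes, including health literacy and empowerment, as missing data.
- Report the number and type of such events by arm.

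The cost is a change of wording and a small amount of extra retrieval from practices. Some questionnaire outcomes will still be missing, and the effect estimate may be somewhat smaller. No stated sample size figure has to change.

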### Practical procedure

General practices will be actively involved in the RCT as follows (see the trial flow chart in Fig. 1). All participating practices will receive a 1-h introduction to the project in their own clinic, conveyed by the first author ([name]) and the staff members will at this time also receive relevant documents for further distribution to patients. At the introduction, the first author will assist the GP in drawing a list from the statistics module of their electronic patient journal. The list will show patients with the hypertension diagnoses K85, K86 and K87 and it will be sorted by central personal register number starting with 1 January.

**Fig. 1 Fig1:**
[figure not shown]
Flow chart

After identifying the list of patients from the statistics module, the practice will review the patients with regards to the inclusion/exclusion criteria. After exclusion, an invitational letter will be sent out to the first 25 patients of those remaining on the list. The invitation will contain a specific appointment for the patient, scheduled for the inclusion consultation with their GP. The invited patients can then opt out or show up at the appointment and receive the oral and written trial participant information (see Additional file 3). The inclusion consultation will be planned before the patients’ expected annual blood pressure consultation and will be planned so they can get blood samples taken at the same time. Thereby patients will not need to go to the practice more times than usual, but the practice will need to conduct an extra GP consultation to give trial information. The participating general practices will be compensated for their extra time spent on consultation with each trial participant and for the extra time spent on reviewing the patient list with regards to inclusion/exclusion criteria.

A few days after the inclusion consultation, the participant will receive an email with a link to a questionnaire (see Additional file 2) that must be completed before the subsequent appointment with the GP. The first page of the questionnaire will be the informed consent form. If the patient answers no to the informed consent, further access to the questionnaire will be closed and the patient will be excluded from the trial.

The GP responsible for the following blood pressure control consultation will ensure that the questionnaire is filled out by the patient. GPs of the intervention group must subsequently guide their patient through YHF on their computer, uploading this individual patient’s data.

With the large number of patients with known hypertension and the compressed method of inclusion, it is expected that GPs will have enough use of the YHF program to maintain the skills and knowledge to use the program, which they will be taught by the research group before start of the project.

The RCT will consist of a 12-month intervention period, except for participants in subgroup Q who will be interviewed six months after enrolment (t_6_) and subsequently excluded. Follow-up for all other patients will happen at the next annual blood pressure control consultation (t_12_) approximately 12 months after registration of baseline data (t_0_).

The intervention group will receive an educational email every two weeks that also includes a reminder of the project and YHF. The first email is sent out approximately two weeks after the initial blood pressure control consultation. The last email is sent out two weeks after the expected one-year follow-up blood pressure control consultation. The emails’ health educational content will reflect available information from the Danish Heart Association’s web page (www.hjerteforeningen.dk).

The GPs are asked to make sure that blood pressures are measured as a standard ambulatory blood pressure just before the annual blood pressure control (t_12_).

### Data collection

Recruitment will take place from summer 2019 until the intended sample size is reached, presumably within 12 months. The RCT is expected to be completed during 2020.

Baseline data will be collected at recruitment (see the SPIRIT figure in Fig.2), via the patient questionnaires and medical records.

**Fig. 2 Fig2:**
[figure not shown]
SPIRIT figure

The questionnaire (q_1_) will include questions to evaluate socioeconomic and sociodemographic variables, baseline health literacy, risk perception and self-efficacy (PAM-13 [15]), smoking status, co-morbidity and medication.

The second patient questionnaire (q_2_) is very short and will be sent out by email approximately two weeks after the first questionnaire and the informed consent has reached the research group. This questionnaire will focus on whether the patient was surprised about the risk score, if any changes in the medication were made and how the general experience of the YHF is. In this email, the intervention group will be informed that they have been selected to receive an email every second week with information about general health literacy, risks of CVD and advice regarding risk reduction.

Six months after enrolment (t_6_) participants will be asked to answer the first questionnaire (q1) again.

Data regarding blood pressure will be obtained through questionnaires at baseline and after the first annual blood pressure control (t_12_), where blood pressure should also be measured as an ambulatory blood pressure. Data regarding number and content of contacts to the GP will be obtained from the patient’s medical records and the affiliated accounting system including prescription databases for estimating compliance. All telephone consultations, email consultations, clinic consultations and home visits are registered. Contacts will be obtained from three years before and up until two years after the intervention.

Patients in the intervention group will receive their personal profile in the YHF to make it possible for them to access and use the program at home in between the blood pressure consultations at their GP. To gain access to their profile from home, they shall use a personal link sent by email at the end of the blood pressure consultation with their GP. All data entered in YHF will be stored in accordance with Danish law by the software provider, with whom a data management agreement has been made.

Baseline measurements of health literacy, perception of risk and PAM-13 will be used (in conjunction with socioeconomic and sociodemographic variables) to identify subgroups of participants. Qualitative data will be obtained via semi-structured interviews, transcribed and analysed with systematic text condensation. The qualitative interviews will seek to shed light on possible explanations for the hypothesised effects on self-management, lifestyle choices, blood pressure and contact with the GP. If possible, the PhD student will personally make all interviews and transcriptions. In case of time constraints, an assistant will carry out part of the qualitative data collection and transcriptions.

### Outcome measures and statistical analysis

For continuous outcomes, i.e. blood pressure and number of GP visits, linear regression analysis of mean changes from baseline will be carried out. Ordinal regression and multinomial regression will be used for ordered and categorical outcomes, i.e. PAM13 score. Adjustments for baseline values will be made. An intention-to-treat analysis will be applied. Subgroup analyses to identify groups that especially benefit from the intervention will be performed.

Since the authors oversee the project throughout and thereby have access to all data as they are generated, analyses on outcome measures will be carried out by a blinded statistician. Data will be delivered pseudonymised to the statistician.

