### Trial design

This study will use a mixed methods approach with a combination of a randomised controlled trial (RCT) and qualitative semi-structured interviews. The protocol has been developed using the SPIRIT checklist as guideline (see Additional file 1).

Participating general practices will be cluster randomised into two groups, an intervention and a control group. The randomisation will be done using REDCap’s randomisation tool. Two general practices will function as pilot practices and be enrolled as if they were intervention practices. In these two practices, patients will be assessed 3–6 months before the project practices. A subgroup Q, of 5–15 patients from the pilot group, will be selected for qualitative interviews.

GPs in the control group will not be introduced to YHF and will follow their patients in the blood pressure control program as usual.

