### Sample size

Calculation of sample size is based on blood pressure as primary outcome. For a two-sample pooled *t* test of a normal mean difference with a two-sided significance level of 0.05, a sample size of 120 participants per group is required. This is to obtain a power of at least 90%, to detect a difference of 5 mmHg between the means at baseline and after one year. To adjust for expected drop-outs, 30 participants will be added per group and at least 300 patients will be enrolled in the trial. To account for cluster-effects when randomising on practice level, the sample size will be further increased by 10%–15% to reach 340 patients. More participants will be needed for subgroup analyses on sociodemographic and, therefore, the aim is to reach a total of 600 participating patients. The pilot practices will provide information regarding the prevalence of patients with inadequately controlled blood pressure willing to participate, as well as more specific knowledge on the needed number of practices included, making the final sample size calculation uncertain at this point.

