### Limitations

It is not possible to control how the GPs act in their own practices. This leaves room for some differences in procedures and information given. This can, however, also be seen as a strength, because the usual care given to the patients by their GP will not be changed. The message drawn from the tool will not be precisely alike for all GPs, but this diversity will reflect real life and that is the goal of the trial – to test whether YHF works in a real-life general practice setting.

Whether patients take the medications they pick up at the pharmacy cannot be controlled. The prescription database should, however, be a reliable reflection of patients’ intake of medicine, since patients presumably take the medications they buy.

The randomisation will be done at GP level instead of patient level. A GP cannot be expected to use the YHF with one patient and not be influenced by the process when the next patient comes. GPs will always intend to give their patients the best treatment they can, but the potential for a spill-over effect is accounted for, by choosing the cluster randomisation process.

The inclusion of GPs will be done by handing out information about the trial and then leaving it up to the GP whether they wish to participate. This might lead to a selection bias, as those willing to participate might have greater interest in hypertension than the GPs not interested in participating. On the other hand, this possible selection bias might give an underestimation of any positive result, if such is to be found, since the participating GPs are possibly already good at treating hypertension.

Use of ambulatory blood pressure measurements will give higher values of blood pressure compared to home blood pressure measurements, but this will only result in a stochastic variance and therefore not influence the outcomes of the trial.

All communication to patients between the consultations is done by email. As reading emails regularly serves as an inclusion criterion, it will potentially exclude some patients with hypertension from participating in the trial. However, given that Denmark has one of the highest levels of Internet coverage of its population, and that all official communication from public institutions to citizens are already sent electronically, it does not seem like a significant challenge.

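### The stated outcome models adjust for baseline only and take no account of practice, the randomised unit; run as written, they understate between-arm standard errors wherever outcomes correlate within practice

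*Protocol article*

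**What the plan says.** On the design, the protocol article is clear. Under Trial design: "Participating general practices will be cluster randomised into two groups, an intervention and a control group". Under Limitations: "The randomisation will be done at GP level instead of patient level", with contamination between patients of the same GP given as the reason. The Participants section plans for 30 GPs, and the Randomisation section numbers the practices 1 to 15 in each of groups A and B.

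The Sample size section starts from a two-sample t test: "with a two-sided significance level of 0.05, a sample size of 120 participants per group is required". It adds 30 per group for drop-out to reach 300. Then, "To account for cluster-effects when randomising on practice level", it adds a further 10%–15% to reach 340. The recruitment aim is 600, to allow subgroup analyses.

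On the analysis, the section Outcome measures and statistical analysis says: "For continuous outcomes, i.e. blood pressure and number of GP visits, linear regression analysis of mean changes from baseline will be carried out". Ordered and categorical outcomes such as the PAM-13 score get ordinal and multinomial regression. The section also names baseline adjustment, intention to treat, subgroup analyses and a blinded statistician. Neither it nor any other section mentions a practice effect, GEE, cluster-robust variance or a practice-level analysis.

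**The concern.** The design and sample size sections accept that patients of one practice are not independent; the analysis section then names models that, in their plain form, assume that they are. A statistician who followed that section literally would treat up to 600 patients as independently randomised when 30 practices were.

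With positive within-practice correlation, the variance of the difference between arms is larger than a patient-level model reports. Intervals are then too narrow, p-values too small, and the error always favours declaring an effect. There is reason to expect some correlation: the Limitations section says that GPs will differ in procedure and in the message that they draw from the tool. A false positive would also have consequences, because the Clinical implications section says that the tool should be rolled out more widely if it significantly improves adherence or reduces hypertension.

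**Working it through.** **Inputs from the protocol.** 30 practices, 15 per arm (Participants, Randomisation). Two-sided alpha 0.05; 120 per group; 30 per group added for drop-out; 10%–15% added for clustering, to 340; aim of 600 (all Sample size). The Randomisation section also mentions 640 patients in 32 practices, which is 20 per practice, the same as 600 in 30. No ICC is given.

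**Reproducing the protocol's figure.** 2 × 120 = 240, and 240 + 60 = 300, which corresponds to 20% loss (240 / 0.80 = 300). Then 300 × 1.10 = 330 and 300 × 1.15 = 345. The stated 340 lies in that range (340 / 300 = 1.133), so the figure reproduces.

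**Formulas**, for equal cluster sizes *m*:
- Design effect: DE = 1 + (*m* − 1) × ICC.
- Reported over true standard error in an unadjusted analysis: 1/√DE.
- Actual two-sided type I error at nominal 5%: 2 × (1 − Φ(1.96/√DE)).

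**Step 1: the protocol's own allowance.** An inflation of 10%–15% is a design effect of 1.10–1.15.
- DE 1.10: 1.96/√1.10 = 1.869, error 6.2%.
- DE 1.133: error 6.6%.
- DE 1.15: 1.96/√1.15 = 1.828, error 6.8%.

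**Step 2: carrying the implied ICC to the recruitment aim.** At 340 patients, *m* = 340/30 = 11.33. The allowance then implies an ICC of 0.10/10.33 = 0.0097 to 0.15/10.33 = 0.0145, about 0.010–0.015. At 600 patients, *m* = 20:
- DE = 1 + 19 × 0.0097 = 1.18, error 7.2%.
- DE = 1 + 19 × 0.0145 = 1.28, error 8.3%.

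**Step 3: an assumed range of ICCs.** With 20 enrolled per practice and 20% loss, *m* = 16 completers:

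| Assumed ICC | DE = 1 + 15 × ICC | Type I error |
|---|---|---|
| 0.01 | 1.15 | 6.8% |
| 0.02 | 1.30 | 8.6% |
| 0.05 | 1.75 | 13.8% |
| 0.10 | 2.50 | 21.5% |

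**Check by simulation.** With 30 clusters of 20 and 20,000 replicates, the unadjusted patient-level test rejected a true null in 7.5% of runs at ICC 0.01 and 16.2% at 0.05. The formula gives 7.2% and 16.1% for that cluster size. A t test on practice means rejected in 5.2% and 5.0% of the same runs. At ICC 0 both tests stayed at about 5%.

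**The case against.** The best defence is that this is silence, not error. The analysis section names model families by outcome type. Linear regression with practice-clustered standard errors is still linear regression, so the wording does not exclude a cluster adjustment. A condensed article commonly leaves the variance estimator and degrees of freedom to the full protocol or SAP, neither of which is shown. The authors plainly know about clustering, since they size the trial for it.

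Much of this stands. A reader might infer that the trial will certainly be analysed as if patients were independent; the document does not establish that, and every figure here is conditional on the text being run as written. The defence does not remove the point, however. The article goes beyond silence: it names the model for each type of outcome and names one adjustment, baseline values. For a cluster-randomised trial, whether the randomised unit enters the model decides whether the test is valid, so it is more than a technical detail.

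A second objection also stands in part. A reader might take an error of 14% or 21% as the expected size. Those values need ICCs of 0.05 and 0.10, which the protocol does not give. Its only anchor is the 10%–15% allowance, which leads to 6.2%–6.8%, or 7%–8% at the recruitment aim. The relevant ICC is that of the baseline-adjusted outcome, which may be lower than that of raw values. It may also differ between outcomes, and the excess is zero where the ICC is zero.

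**Conclusion.** The point holds, on condition that the analysis section is run as written. The stated method does not fit the stated design, and it contradicts the protocol's own expectation of cluster effects. The excess is modest at that expected level: about 6.2%–6.8% instead of 5%, rising to about 7%–8% if the implied ICC of 0.010–0.015 holds at 20 patients per practice. It becomes large only at ICCs of about 0.05 and above, which are assumptions. The figures rest on equal cluster sizes, 30 practices and the normal approximation. The point should be settled before analysis, because it touches the between-arm comparison of every outcome that correlates within practice, and because the repair is cheap. If the full protocol or SAP already accounts for practice, the published section need only say so.

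**What to change.** In Outcome measures and statistical analysis, state that all between-arm outcome models (linear, ordinal and multinomial) account for the randomised practice, identified by its TGN. Either a practice random intercept, or GEE or cluster-robust variance, would do, with a small-sample correction suited to about 30 clusters. Keep the baseline adjustment. The choice among these valid methods can be left to the trial statistician, provided it is fixed before analysis. The distribution used for the number of GP visits is a separate question.

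The cost is a sentence or two and somewhat wider intervals; no data collection changes. Power should survive. The protocol gives no SD, but 120 per group, 5 mmHg and 90% power imply about 11.9 mmHg, which is taken here as an assumption. With 20% loss and the design effect applied (normal approximation), 600 patients give 240 × 1/1.15 = 209 effective patients per arm at ICC 0.01 and 240 × 1/1.75 = 137 at ICC 0.05, for power of about 99% and 94%. With 340 patients, power is about 92% and 83%.
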